### Data monitoring and management

The data monitoring committee (DMC) 's responsibilities include safety monitoring, test data monitoring and test design adjustment recommendations with no conflicts of interest. Rehabilitation Department of Tongji Hospital will be in charge of informed consent quality assurance, eligible participant recruiting, implementation of interventions, and data administration. Designated person will be responsible for collecting case report forms (CRFs) as well as data transfer and analysis. The investigator and director are responsible for retaining all records, and the data center will keep anonymized case report form data. Electronic data will be preserved on password-protected computers, while all paper data will be kept in secure filing cabinets.

### Statistical analysis

The SPSS 21.0 program will be used for all statistical analysis and the significance level set for all the analysis will be *P* ≤ 0.05. The Shapiro-Wilk test will be used (*P* > 0.05) to check normality. In this study, Continuous variables will be expressed as mean with standard deviation and median for non-normal distributions and categorical variables will be presented as percentage or frequencies. Between the three groups, data will be first compared using Student's *t*-test for continuous variables and the chi-square or Fisher's exact tests for categorical variables. Appropriate metrics will be processed further using repeated measures ANOVA. Bonferroni correction method and False Discovery Rate <5% will be considered for multiple comparisons. All analyses will be done with the intention to treat principle, and missing data will be estimated using multiple imputation. The mean comparisons for related outcomes in two different moments will be studied with the Wilcoxon-signed rank test. The major strategy for dealing with missing data will be a sensitivity analysis and weighted estimating equations.

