## Methods and analysis

### Study design

The study will be a non-blinded pilot randomized controlled trial with three parallel groups. The study will be performed in accordance with the Declaration of Helsinki. This protocol follows the Consolidated Standards of Reporting Trials (CONSORT) Statement on randomized trials and it will be conducted according to the Recommendations for Interventional Trials (SPIRIT). The trial was registered in the Chinese Clinical Trial Registry (No. 2200060885). It will be carried out in the Department of Rehabilitation Medicine of Tongji Hospital in Wuhan, China. A flowchart overview of the study is presented in Figure 1. The Standard Protocol Items: SPIRIT table for enrolment, interventions, and assessments is presented in Table 1. Forty-five eligible subjects will be randomly allocated into three groups equally: (1) sham-cTBS group, (2) cTBS-cM1 group (cTBS targeting contralesional M1), (3) cTBS-cPMA group (cTBS targeting contralesional PMA).

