### Randomization and blinding

The physician will screen out the patients who meet the eligibility criteria, explain the whole content of the trial and ask the consent to sign the informed consent. Their demographic information, medical history, and medication details will then be collected. We will use an electronic random sequence generator (www.random.org) to randomly assign all of the individuals to one of the three groups in a 1:1:1 ratio. An independent researcher will conceal the allocation using sealed and opaque envelopes, numbered consecutively. In this trial, subjects, assessors, and data analysts are blind to the allocation results. Because this study involves locating therapeutic targets in the cerebral cortex, the intervenor cannot be blind. The treatment and outcome evaluation regimen are depicted in Table 1.

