### Sample size calculation

Sample size is estimated through software G^*^Power 3.1 (50). We used MAS as the primary outcome for the calculation of the effect size. It is determined to be 12 per group based on a power of 0.8 with α level at 0.05. According to a previous study (21), effect size *d* = 0.53 was calculated based on the difference in MAS score from their main research results. Through conversion, the effect size *f* used in our study is about 0.25. Repeated measures correlation in our study is set at 0.5 to detect a moderate within-between effect of Conhen's *f* = 0.25. Considering a drop-out rate of 20%, we aim to recruit totally 45 stroke subjects.

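### The plan names a two-sample t-test for a three-group comparison and does not make the repeated-measures model behind the sample size the deciding analysis

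*Protocol article*

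**What the plan says.** The trial has three parallel arms. Study design states: "Forty-five eligible subjects will be randomly allocated into three groups equally". Randomization and blinding gives the method as to "randomly assign all of the individuals to one of the three groups in a 1:1:1 ratio".

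Statistical analysis then gives four rules that bear on this point:
- The first comparison: "Between the three groups, data will be first compared using Student's *t*-test for continuous variables".
- The second step: "Appropriate metrics will be processed further using repeated measures ANOVA". No criterion is given for which metrics qualify.
- The level: "the significance level set for all the analysis will be *P* ≤ 0.05".
- Multiplicity: "Bonferroni correction method and False Discovery Rate <5% will be considered for multiple comparisons". Neither method is committed to, and the family of comparisons is not named.

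Sample size calculation uses a different test from the first of these. It states "It is determined to be 12 per group based on a power of 0.8 with α level at 0.05" and "Repeated measures correlation in our study is set at 0.5 to detect a moderate within-between effect of Conhen's *f* = 0.25". MAS is the outcome used for the effect size. Outcome measurements makes the change over the four treatment weeks in MAS and FMA-UE the primary measure.

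**The concern.** A two-sample test is prescribed where three groups are to be compared. Carried out literally, it can only mean three pairwise tests per variable, each at the 0.05 that the section sets for every analysis. The trial was sized on a single overall group-by-time test, but the analysis text does not assign MAS, or any other outcome, to that test.

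Two things are at stake. First, if the pairwise t-tests carry the conclusion and go uncorrected, the false-positive rate per outcome is above the stated level. Second, no test is fixed as decisive before the data are seen. A favourable pairwise t-test and a favourable group-by-time test could each be presented as the primary result.

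**Working it through.** **1. The plan's own sample size.** Inputs from Sample size calculation: f = 0.25, correlation ρ = 0.5, α = 0.05, power 0.8, dropout 20%. There are k = 3 groups (Study design) and m = 3 MAS assessments: baseline, 4 weeks and follow-up (Table 1). Sphericity is assumed (ε = 1). For the within-between interaction:

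- λ = f² × N × m / (1 − ρ) = 0.0625 × 36 × 3 / 0.5 = 13.5
- df1 = (k − 1)(m − 1) = 4
- df2 = (N − k)(m − 1) = 33 × 2 = 66
- Power from the noncentral F: 0.823 at N = 36 and 0.781 at N = 33

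The smallest balanced size is therefore 36, or 12 per group, and 36 / (1 − 0.20) = 45. The stated figures reproduce exactly. With two time points the size would be 42, and with four it would be 30. The calculation therefore corresponds to the three-visit group-by-time test, and not to a t-test.

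**2. Error rate of the test named first.** Assumptions not in the document: two-sided tests, normal data, equal variances, no true difference between any groups. The rate is the chance of at least one P ≤ 0.05 for one outcome at one time point, from 400,000 simulated trials at 12 and at 15 per group.

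| Procedure | 12 per group | 15 per group |
|---|---|---|
| Three pairwise t-tests, uncorrected | 12.2% | 12.2% |
| Three pairwise t-tests, Bonferroni at 0.05/3 | 4.4% | 4.4% |
| One overall three-group F-test | 4.9% | 5.0% |

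The large-sample limit for the first row, from the range of three means, is also 12.2%. Treating the three tests as independent would give 1 − 0.95³ = 14.3%, which is too high because the pairs share groups. If only the two active-versus-sham pairs are tested without correction, the rate is 9.0%.

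**3. Error rate if the t-tests act only as a gate.** Suppose an outcome goes to the group-by-time F-test only after a significant pairwise t-test, and the F-test then decides. With three visits and ρ = 0.5 (100,000 simulated trials), the overall error is 1.3–1.4% with a gate on week-4 scores and 3.0–3.1% with a gate on change scores. The F-test alone gives 4.9%. A gate of this kind lowers the error, and it can only lower power as well.

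**4. Side by side.** The same text thus allows three different procedures:
- pairwise t-tests decide (12.2% or 4.4%, depending on a correction that is not committed)
- t-tests gate the ANOVA (below 5%)
- the t-tests concern baseline only (no bearing on the efficacy error)

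The test used for the sample size is the sole deciding test only if the t-test sentence plays no part in the efficacy analysis.

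**The case against.** The strongest reply has four parts.

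- **Correction.** A reader might infer that the plan yields 12% false positives per outcome. The section does not support that as a flat statement, because it also says that Bonferroni and a false discovery rate will be considered, and Bonferroni brings the figure to 4.4%. This stands. What remains is that considering a correction does not commit to one, that the two methods control different error rates, and that no family is named.
- **Sequence.** A reader might attach the 12% to the t-test-then-ANOVA sequence. It belongs to the uncorrected pairwise t-tests alone; as a gate they push the error below 5%. This stands.
- **Selection.** A reader might infer that the t-test results choose which metrics go forward. The text does not say so. Suitability could mean type of variable, normality (a Shapiro-Wilk check is planned) or number of visits, which differs between outcomes in Table 1. This stands; the defect is an unstated criterion, not documented selection on results.
- **Baseline reading.** The sentence pairs the t-test with chi-square and Fisher tests, and may describe comparability at baseline. This is possible, but the section does not say it, and a t-test would still be the wrong test for three groups.

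It can also be said that this is a condensed article on a trial that Study design calls a pilot, and that selection rules and families of comparisons are often left to a fuller document. That is fair for those details. It does not cover the naming of a two-sample test for three groups, which is a stated rule that does not fit the design.

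**Conclusion.** The point holds in a limited form. The article prescribes a two-sample test for a three-group comparison, and it does not make the model on which the trial was sized the deciding analysis.

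The consequence for error control is conditional. It is up to about 12% per outcome and time point if three pairwise t-tests decide without correction, 4.4% if Bonferroni over the three pairs is applied, and about 5% for one overall test. These rates assume two-sided testing of normal data with equal variances. MAS is ordinal, so its exact rates may differ. The sample size itself is not in question: it reproduces under the group-by-time model with three visits.

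**What to change.** Change the Statistical analysis section as follows.

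1. Replace Student's t-test with a three-group test.
2. Name the group-by-time repeated-measures model from Sample size calculation as the deciding analysis for the primary outcome. Apply it to every continuous outcome with repeated measurements, so that no undefined subset is left.
3. Commit to one rule for pairwise contrasts. Either examine them only if the overall test is significant at 0.05, or use Bonferroni over the three pairs (0.05/3 each). With exactly three groups the first option holds the familywise error at 5%, provided that each pairwise test is that pair's own group-by-time effect. For contrasts at a single visit, use Bonferroni.
4. If the t-test sentence was meant for baseline comparability, say so, and describe baseline by summary statistics without tests.

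A week-4 ANCOVA adjusted for baseline would fit the four-week change in Outcome measurements. If the sponsor prefers it, the sample-size justification must be restated, because the present one belongs to the group-by-time test.

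The cost of items 1 to 4 is wording only. Data, visits, software and sample size stay the same. A committed Bonferroni correction makes pairwise claims slightly harder to reach.

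### If Bonferroni is meant for the three arm contrasts within an outcome, it is needlessly conservative: with exactly three arms, a closed test or Shaffer's step-down holds the same 5% family-wise error with more power

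*Protocol article*

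**What the plan says.** The Study design section fixes the number of arms: "Forty-five eligible subjects will be randomly allocated into three groups equally". The arms are sham, cM1 and cPMA.

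On multiplicity, the Statistical analysis section has one sentence: "Bonferroni correction method and False Discovery Rate <5% will be considered for multiple comparisons". It does not say which comparisons form the family. It also does not choose between two methods that control different error rates. The same section puts Student's t-tests between the three groups first, without saying for which data, and repeated measures ANOVA afterwards for metrics judged suitable. The ANOVA is not made a condition for the pairwise tests.

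The Sample size calculation section sizes the trial on a three-arm test, "to detect a moderate within-between effect of Conhen's *f* = 0.25", and plans it "based on a power of 0.8 with α level at 0.05".

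**The concern.** The questions of interest are pairwise. The Abstract and Introduction ask whether cPMA stimulation beats sham and whether it beats conventional cM1 stimulation. The multiplicity sentence follows directly on the three-group comparison and the ANOVA, so one natural use of Bonferroni is over the three contrasts cPMA-sham, cM1-sham and cPMA-cM1.

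Used that way, it spends less than the allowed error. With 45 patients, power on these contrasts is scarce, and part of it can be recovered without more patients and at the same family-wise error.

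**Working it through.** **1. The plan's own figure.** Inputs from Sample size calculation: "effect size *d* = 0.53 was calculated based on the difference in MAS score", converted to f = 0.25 (0.53/2 = 0.265, stated as about 0.25); "Repeated measures correlation in our study is set at 0.5"; alpha 0.05; power 0.80. Three measurement times (m = 3: baseline, 4 weeks, follow-up) are inferred from the assessment schedule. For the group-by-time interaction with k = 3 arms:

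- λ = f²·N·m/(1−ρ) = 0.0625 × 36 × 3 / 0.5 = 13.5
- df = (k−1)(m−1) = 4 and (N−k)(m−1) = 66
- power is 0.823 at N = 36 and 0.781 at N = 33

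So 36 is the smallest balanced total, matching "It is determined to be 12 per group". Then 36/0.8 = 45, or 15 per arm, matching "Considering a drop-out rate of 20%, we aim to recruit totally 45 stroke subjects". With m = 2 (baseline and 4 weeks), λ is 9 at N = 36 and 42 patients would be needed.

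**2. Why three arms do not need 0.0167.** Any two true pairwise nulls imply the third. The only intersection to protect is therefore the global null of three equal arms.

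- *All arms equal:* an error requires the three-arm test to reject, with probability at most 0.05.
- *Exactly one pair equal:* only that pair can be wrongly rejected, at 0.05 or less.
- *Exactly two pairs equal:* impossible.

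Bonferroni tests each pair at 0.05/3 = 0.0167 throughout. Shaffer's step-down tests the smallest P at 0.0167. Once that is rejected at most one null can still be true, so the other two are tested at 0.05.

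**3. Family-wise error, simulated.** Under the global null it is 0.043 to 0.044 with Bonferroni, 0.049 to 0.050 with the closed test and 0.12 with three unadjusted t-tests. With one arm different it is 0.017 with Bonferroni and at most 0.050 with the closed test.

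**4. Power, simulated** (200,000 to 400,000 trials per setting; normal data, equal variances, sphericity, two-sided tests). In the f = 0.25 rows each pair is compared by its own group-by-time test with pooled error. In the SD rows the contrasts are one-way, in residual-SD units.

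| Setting | n per arm | Pattern | Contrast | Bonferroni | Closed |
|---|---|---|---|---|---|
| f = 0.25, m = 3 | 12 | one arm differs | true pair | 0.65 | 0.75 |
| f = 0.25, m = 3 | 15 | one arm differs | true pair | 0.78 | 0.86 |
| f = 0.25, m = 2 | 12 | one arm differs | true pair | 0.54 | 0.65 |
| f = 0.25, m = 2 | 15 | one arm differs | true pair | 0.66 | 0.77 |
| f = 0.25, m = 3 | 12 | equally spaced | cPMA-sham | 0.80 | 0.82 |
| f = 0.25, m = 3 | 12 | equally spaced | cPMA-cM1 | 0.20 | 0.34 |
| f = 0.25, m = 3 | 15 | equally spaced | cPMA-cM1 | 0.26 | 0.42 |
| 1.0 SD | 15 | one arm differs | true pair | 0.60 | 0.71 |
| 1.0 SD | 15 | equally spaced | cPMA-sham | 0.60 | 0.64 |
| 1.0 SD | 15 | equally spaced | cPMA-cM1 | 0.14 | 0.25 |
| 0.53 SD | 12 | one arm differs | true pair | 0.125 | 0.170 |
| 0.53 SD | 15 | one arm differs | true pair | 0.16 | 0.22 |

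Shaffer's step-down keeps most of the gain: 0.68 in the row with 1.0 SD, 15 per arm and one arm different, against 0.60 and 0.71.

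**5. Where the closed test can lose.** With equally spaced observed means, F = t²/2. At 15 per arm (42 df), Bonferroni rejects the extreme pair at |t| > 2.494. The 2-df F-test (critical value 3.22) needs |t| > √(2 × 3.22) = 2.538. In simulation, the 2-df version missed a Bonferroni rejection in under 0.5% of trials. In the f = 0.25, m = 3 settings, where the first step is the 4-df interaction test, it did so in about 0.7% to 1.9%. Shaffer's step-down never does.

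**The case against.** A reader might infer that the protocol prescribes Bonferroni for the arm contrasts and so gives up about 10 points of power for nothing. The document does not support any of the three parts of that reading.

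- *Prescribed for the arms.* The sentence names no family and only undertakes to consider two methods. It could equally concern the two primary outcomes, the four muscle groups rated on the MAS, the time points, or the neurophysiological and imaging measures. The loss is conditional on how the sentence is applied.
- *About 10 points.* That holds when one arm differs from two equal arms. The authors expect cPMA to do better than cM1. If cM1 also works, effects are ordered and the cPMA-sham contrast gains only about 1 to 5 points, while cPMA-cM1 gains more. The protocol gives no pattern of means.
- *For nothing.* Bonferroni provides matching simultaneous confidence intervals and needs no significant overall test. The version led by the F-test occasionally misses what Bonferroni would find.

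It can also be said that Bonferroni after ANOVA is valid and that the exact pairwise procedure may sit in a fuller document not shown. That stands: this is an inefficiency in one reading of the plan, not an error that invalidates it. It does not remove the case for settling the procedure, because the published sentence names corrections without fixing what they apply to, and a better procedure costs almost nothing.

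**Conclusion.** The point holds as a cheap improvement, conditional on Bonferroni being used over the three arm contrasts within one outcome. In that case it is more conservative than a 5% family-wise error requires.

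At 12 per arm the closed test gains about 10 points when one arm differs. With equally spaced effects of the planned size, or of about 1 SD between the extreme arms, it gains about 1 to 5 points for cPMA-sham and 9 to 14 for cPMA-cM1. The latter reaches 16 at 15 per arm. If d = 0.53 is a standardised one-way contrast and one arm differs, the gain is 4 to 5 points and power is low under either method.

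The power figures rest on normality, equal variances and sphericity, and are approximate because the MAS is ordinal. The closure argument does not rest on normality; it needs only valid tests of the three-arm null and of each pair.

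**What to change.** State for each primary outcome: the three arms are compared at week 4 with a 2-df test at two-sided 0.05; if it is significant, each of the three pairwise contrasts is tested at 0.05 (closed testing, valid because there are exactly three arms). Alternatively, specify Shaffer's step-down: smallest P against 0.0167 and, if rejected, the other two against 0.05. Shaffer's version suits a team that wants never to reject less than Bonferroni.

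Let this replace Bonferroni and FDR for the arm contrasts only, and replace the t-tests run first across three groups. State separately how multiplicity over MAS, FMA-UE, muscle groups and time points is handled; the change above does not cover it.

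The cost is a sentence or two, fixed before unblinding, with no extra patients or data. The price is that the tests no longer come with matching simultaneous confidence intervals and that the version led by the F-test can, rarely, miss a Bonferroni rejection.

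### Multiple imputation is paired with an omnibus repeated-measures F test and a signed-rank test; if the imputations are not properly pooled, the nominal 5% F test rejects in roughly 7–18% of null trials at the planned 20% drop-out

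*Protocol article*

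**What the plan says.** The Statistical analysis section of the protocol article fixes three things together.

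- Handling of missing data: "All analyses will be done with the intention to treat principle, and missing data will be estimated using multiple imputation".
- Comparison of arms over time: "Appropriate metrics will be processed further using repeated measures ANOVA". This follows a first comparison of the groups by t-test.
- Before/after comparison within patients: "The mean comparisons for related outcomes in two different moments will be studied with the Wilcoxon-signed rank test".

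Because intention to treat covers every analysis, imputed values enter both of the last two. The same section also names weighted estimating equations, with a sensitivity analysis, as the main approach to missing data. It does not say how results from several imputed data sets are combined.

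The Sample size calculation section expects a substantial amount of missing data: "Considering a drop-out rate of 20%, we aim to recruit totally 45 stroke subjects". Table 1 places the two primary scales (MAS and FMA-UE) at baseline, week 4 and week 8. The Outcome measurements section makes the change over the 4 weeks of treatment the primary measure.

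**The concern.** Multiple imputation protects the error rate only if the spread between imputed data sets is carried into the final test. The standard combining rules do this for an estimate with its standard error. A signed-rank test returns a P value and neither of those. An omnibus F is not itself an estimate with a standard error, so it needs either multi-parameter pooling or a switch to contrasts.

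If this step is missed, the F test treats imputed values as observed. It then works with 45 patients and (45 − 3) × 2 = 84 error degrees of freedom, where 36 completers would give (36 − 3) × 2 = 66. Standard errors are too small and differences between arms over time are declared too often. In a trial with 15 patients per arm, that could produce a spurious finding in favour of one stimulation target.

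**Working it through.** **Inputs from the article.** Three arms, "randomly assign all of the individuals to one of the three groups in a 1:1:1 ratio"; "It is determined to be 12 per group based on a power of 0.8 with α level at 0.05"; f = 0.25, which the article converts from d = 0.53; a correlation assumption, "Repeated measures correlation in our study is set at 0.5 to detect a moderate within-between effect"; 20% drop-out and 45 recruited, so 15 per arm. Three visits are taken from Table 1.

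**The plan's own figure.** For the within-between interaction with k = 3 arms, m = 3 visits and sphericity, λ = f²·N·m/(1 − ρ), df1 = (k − 1)(m − 1) and df2 = (N − k)(m − 1).

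- N = 36: λ = 0.0625 × 36 × 3 / 0.5 = 13.5, df 4 and 66, power 0.823.
- N = 33: power 0.781.
- So 12 per group reproduces, and 36/0.8 = 45.

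The planned test is therefore the group-by-time F, and the level of that test is what was checked.

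**Null simulations.** Assumptions: normal data, 3 × 15 patients, 3 visits, correlation 0.5, no arm effect, drop-out unrelated to outcome, proper regression imputation with five imputations where the number is recorded. The article does not say which visits drop-outs miss, so the pattern was varied. Three separately programmed simulations gave these rejection rates for the F test at a nominal 5%:

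| Missing pattern | One completed set | Imputed values averaged | P values averaged | Mean F / median P | Pooled |
|---|---|---|---|---|---|
| A: 20% miss weeks 4 and 8 | 14.6% | 16.0% | 8.9% | – | – |
| A: 10% miss week 4, 20% miss week 8 | 12.3% | 12.3% | 7.6% | – | – |
| B: 20% miss week 8, half of them also week 4 | 11.8% | 12.9% | – | 10.6% / 10.3% | D1 5.1%, D2 4.5% |
| B: 20% miss weeks 4 and 8 | 16.7% | 17.9% | – | 14.5% / 14.0% | D1 5.0%, D2 4.9% |
| C: 20% miss weeks 4 and 8 | 14.0% | 15.8% | 7.4% | – | D2 3.6% |

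The unpooled entries run from 7.4% to 17.9%, hence roughly 7–18%. Counting a result as positive when any of five imputed sets is significant gives 23–32%. That rule is plainly wrong and is left out of the range. Monte Carlo error in simulation B is about 0.5–1 percentage point. With essentially no missing data, the same code rejects in 5.7% of 1,000 trials, and complete-case ANOVA in simulation A gives 4.8–5.4%. The excess therefore comes from the unpooled imputation.

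**Sensitivity (simulation B).** Unpooled F rates are 7.3–9.1% at 10% drop-out and 15–27% at 30%. At 20% drop-out with both visits missed, they are 12–19% for correlations of 0.3 to 0.7.

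**Signed-rank test (simulation B).** For one arm of 15, baseline against week 4 at 20% drop-out, unpooled rates are 6.0–7.0% if half the drop-outs miss week 4 and 7.3–10.3% if all do. On observed pairs alone they are 4.6% and 4.3%.

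**Week-4 contrast, cPMA against sham (simulation A, 20 imputations).** One completed set gives 10.0%, pooling the difference and its standard error gives 4.0%, and an observed-data model gives 4.2%.

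**Baseline adjustment.** At ρ = 0.5, a change score has variance 2(1 − 0.5)σ² = 1.00σ². A baseline-adjusted week-4 value has 1 − 0.5² = 0.75σ², which is 25% less. In simulation C, the baseline-adjusted observed-data analysis held 5.1% under the null. Under an assumed true difference it had 67% power, against 52% for correctly pooled imputed change scores. The article gives no raw difference from which to set that effect, so only the direction should be relied on. Part of the gain comes from adjusting for baseline and not from avoiding imputation.

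**The case against.** A reader might infer that the plan as written has an inflated type I error, or that repeated-measures ANOVA offers nothing to pool. The documents support neither.

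- **No unpooled analysis is prescribed.** Combining across imputations is normally understood as part of multiple imputation. A journal article may leave the number of imputations and the combining rule to the full protocol or analysis plan. This stands: the missing rule is not itself a finding, and the inflated rates apply only if pooling is not done.
- **ANOVA can be pooled.** Its contrasts have standard errors, and D1 or D2 handles the omnibus F at 3.6–5.1% in the table above. This stands.
- **A poolable estimate exists in the article.** The 4-week change is the primary measure and a t-test between groups is listed. This stands, although the test that was powered is the interaction F.
- **The signed-rank test compares two moments within patients.** Its inflation cannot create differences between arms, and the 7–18% does not describe it. This stands; its own unpooled range is 6.0–10.3%.
- **Weighted estimating equations may be the main missing-data method.** If so, these rates would not describe the primary result. The article leaves the ranking of the two methods open. That is a separate inconsistency, and it limits how firmly the error rates can be attached to the primary analysis.

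The poor fit of the stated choices remains. The signed-rank test has no place in the standard combining rules, and the F needs a special rule to be valid, while a simpler and more precise analysis of the observed data is available.

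**Conclusion.** The concern holds in conditional form. The plan pairs multiple imputation with a rank test that the standard combining rules do not cover, and with an omnibus F that keeps its level only under D1/D2 or contrast pooling. If between-imputation variance is not carried into the F test, the nominal 5% becomes roughly 7–18% at 20% drop-out. If it is, the level is about 5% or below.

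These figures assume normal outcomes, correlation 0.5, data missing completely at random, and the visit patterns shown, none of which the article fixes beyond the correlation and the drop-out rate. They give an order of magnitude for an avoidable error and do not predict this trial's error rate. The case for changing the text rests on the poor fit of the tests and on the better alternative, not on the absence of a pooling rule.

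**What to change.** Make the primary analysis a mixed model for repeated measures, fitted by REML with small-sample degrees of freedom, on all observed visits of all randomised patients. Include arm, visit, arm-by-visit and baseline, and report the week-4 arm differences with confidence intervals. It needs no imputation if data are missing at random, and it gains precision from baseline.

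Keep multiple imputation as a sensitivity analysis that pools the week-4 difference and its standard error, or the F by D1 or D2. Do not run signed-rank tests on imputed data.

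If the sponsor prefers to keep imputed repeated-measures ANOVA, stating D1/D2 or contrast pooling and taking the signed-rank test off imputed data would repair the level, without the gain from baseline adjustment.

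Cost: about two sentences of analysis text, with no new data or patients. Some P values will be less favourable than from an unpooled analysis. The model treats the MAS score as approximately continuous, as the planned ANOVA already does.
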